**Methods:**

We will conduct a randomized controlled clinical trial (ClinicalTrials.gov registration pending) comparing a 3-session SFBI (experimental group) with a single session of brief counselling as usual care (control group) in primary care. Interventions will be delivered in person by a psychologist or social worker. A total of 320 participants are expected to be recruited during preventive routine checkups using the Alcohol, Smoking, and Substance Involvement Screening Test. Participants reporting intermediate- to high-risk substance use on this screening tool will be randomly assigned to each group. Research assistants will administer instruments at baseline and at 3-, 6-, and 9-month follow-ups and will be blinded to the assigned treatments. The primary outcome assessed will be substance use patterns, while secondary outcomes include background information, depressive symptoms, anxiety symptoms, and motivation for treatment. Statistical analyses, including *t* tests, ANOVA, and Fisher exact tests will be conducted depending on variable type and normality. A qualitative component to assess acceptability and pertinence will include focus groups with participants and practitioners, followed by a content analysis.

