### Sample Size

The necessary sample size was calculated considering the minimum effect size found in evidence-based psychosocial interventions for substance use disorders (Cohen *d*=0.24 for polysubstance use, equivalent to Cohen *f*=0.12) [35]. The calculation was performed using the G*Power (Heinrich-Heine-Universität Düsseldorf) statistical software for sample size calculation [36], considering 80% power and a significance level of 5%. For the interaction effect between within-subject and between-subject factors in mixed ANOVA (details available in the Analysis Plan section), a sample size of 96 individuals was obtained, and after considering a 40% attrition rate [24,35] in follow-up, it increases to 160 individuals. The evaluation of the SFBI will be conducted separately by substance type (evaluating its effectiveness separately for at least alcohol, cocaine, and cocaine base paste, considering possible overlaps between them and marijuana). Thus, we plan to recruit 320 participants.

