### Analysis Plan

For quantitative-specific objective 3, we will use the standard *P*<.05 criterion to make inferences. Tests to detect any potential differences between individuals who received interventions from either social workers or psychologists will be conducted. The analysis approach for each specific objective is described in the following sections.

#### Specific Objective 1

The first specific objective aims to determine whether the SFBI reduces substance use patterns and risk-level substance use of participants at the 3-month, 6-month, and 9-month follow-ups (post baseline). A descriptive analysis of the recorded variables will be conducted for each participant in the experimental group, pretreatment, and at 3 months, 6 months, and 9 months post baseline. Minimum and maximum values will be reported, and the normality of their distribution will be assessed using frequency histograms and the Shapiro-Wilk normality test. Categorical variables will be described using absolute and percentage frequencies. For individuals participating in the experimental group, the following analyses will be conducted separately at each posttreatment measurement (3 months, 6 months, and 9 months): the change in frequency and quantity of consumption according to the TOP instrument will be calculated for each participant, with the mean change and its corresponding CI estimated, and a paired repeated-measures ANOVA conducted to evaluate whether there is a significant treatment effect on the average weekly consumption; if the normality assumption is not met, the nonparametric Wilcoxon signed-rank test will be used. In addition, the percentage of individuals who decrease their risk category will be calculated, and their respective CIs estimated, and, since the TOP contains categorical items, the McNemar test will be applied to evaluate whether significant changes occurred.

#### Specific Objective 2

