The third specific objective aims to determine whether participants receiving the SFBI improve their substance use patterns, substance use risk level, consequences of substance use, and mental health symptoms as compared with those receiving a minimal intervention. A descriptive analysis of the recorded variables will be conducted for each participant in both experimental and control groups at baseline and at 3 months, 6 months, and 9 months post baseline. Quantitative variables will be described using mean, SD, median, minimum, and maximum values, and their distribution normality will be assessed using frequency histograms and the Shapiro-Wilk normality test. Categorical variables will be described using absolute and percentage frequencies. For each posttreatment measurement (3 months, 6 months, and 9 months), the following analyses will be conducted: the change in substance use patterns and substance use risk level (TOP) will be calculated for each participant in both experimental and control groups, and the mean with its corresponding CI will be estimated; the change in the PHQ-9 score will be calculated for individuals in both experimental and control groups, and the mean with its corresponding CI will be estimated; the change in the GAD-7 score will be calculated for individuals in both experimental and control groups, and the mean with its corresponding CI will be estimated. Baseline characteristics, including demographic background and sociofamilial situation, of participants in the control and experimental groups will be compared, with *t* tests or Wilcoxon-Mann-Whitney tests used for quantitative variables when the normality assumption is unmet, and the Fisher exact test used for categorical variables. Given that this is a superiority design, 1-tailed tests will be used for the following comparisons. The mean decrease in monthly consumption will be compared between individuals in the experimental and control groups using a mixed ANOVA, with group (experimental and control) as the between-subjects factor and time of measurement (pretreatment, 3 months, 6 months, and 9 months) as the within-subjects factor. Similarly, mean PHQ-9 scores will be compared between the two groups using a mixed ANOVA, with group (experimental and control) as the between-subjects factor and time of measurement (pretreatment, 3 months, 6 months, and 9 months) as the within-subjects factor, with the Friedman-aligned ranks test applied if the variable normality assumption is unmet. Finally, the percentage of individuals who decrease their substance use patterns and risk (TOP) will be compared between the experimental and control groups, using the Fisher exact test.

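### If PHQ-9 fails a normality check, the between-arm mixed ANOVA gives way to a rank test that, in its usual form, does not compare the arms

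*Protocol article*

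**What the plan says.** The Abstract (Methods) gives a general rule: the statistical analyses "will be conducted depending on variable type and normality". The Analysis Plan then applies it unevenly.

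- **Specific Objective 1, consumption within the SFBI arm.** A repeated-measures ANOVA is planned at each follow-up, but "if the normality assumption is not met, the nonparametric Wilcoxon signed-rank test will be used".
- **Specific Objective 2, PHQ-9 within the SFBI arm.** Normality is examined, but the repeated-measures ANOVA follows without a condition.
- **Specific Objective 3, between arms.** For quantitative variables "their distribution normality will be assessed using frequency histograms and the Shapiro-Wilk normality test". Monthly consumption is compared by a mixed ANOVA (group by four measurement times), and that sentence names no alternative. The next sentence gives PHQ-9 the same mixed ANOVA, with the Friedman aligned-ranks test "applied if the variable normality assumption is unmet". No gated test is written for GAD-7.

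The Sample Size section bases the trial on one of these analyses: "For the interaction effect between within-subject and between-subject factors in mixed ANOVA", "a sample size of 96 individuals was obtained".

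**The concern.** There are three difficulties, in order of weight.

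1. **The PHQ-9 fallback answers another question.** The comparison of interest is whether the arms change differently over time. The mixed ANOVA tests this through the group-by-time interaction. The Friedman aligned-ranks test is a test for repeated measures in blocks. With participants as blocks and visits as conditions it asks whether scores differ between visits. PHQ-9 may well fall in both arms after screening and counselling, and the test would then be significant without any treatment effect.
2. **The check looks at the wrong quantity.** ANOVA's normality assumption is about residuals. A bounded sum score or a 28-day count can look non-normal while the F test behaves acceptably. Shapiro-Wilk also gains power with sample size, so it rejects more readily just when the mean-based test needs normality less.
3. **The rule is not settled for consumption between arms.** The Abstract makes tests depend on normality in general, but Objective 3 attaches the fallback only to PHQ-9. An analyst could defend either reading after seeing the data.

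At stake is a false between-arm conclusion on depressive symptoms, a secondary outcome, and an avoidable choice on the consumption comparison.

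**Working it through.** **Step 1. Reproduce the plan's own figure.** Inputs from Sample Size: "Cohen *d*=0.24 for polysubstance use, equivalent to Cohen *f*=0.12", 80% power, 5% significance. From Objective 3: g = 2 groups and m = 4 times. Assumed, because not stated: within-person correlation ρ = 0.5 and sphericity (ε = 1).

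- λ = f²·N·m/(1−ρ) = 0.0144 × 96 × 4/0.5 = 11.06
- df1 = (g−1)(m−1) = 3; df2 = (N−g)(m−1) = 94 × 3 = 282
- Power = 0.8002, so N = 96; with 40% attrition, 96/0.60 = 160.

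Both stated figures reproduce. With ρ = 0.3 the N would be 134, and with ρ = 0.7 it would be 60. The sizing therefore belongs to the mixed ANOVA interaction.

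**Step 2. How often would the check fail?** The protocol gives no outcome distributions, so these are simulated under assumption, with Shapiro-Wilk at 0.05.

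| Assumed variable | n = 48 | n = 96 |
|---|---|---|
| PHQ-9 sum, mean 2.5-7 | 79-100% | about 100% |
| PHQ-9 sum, mean about 9.5 | 36-72% | 79-99% |
| PHQ-9 sum, mean about 12 | 11-32% | 33-85% |
| Use in past 28 days, several skewed shapes | 75-100% | 99-100% |

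A PHQ-9 distribution assumed to be nearly normal (mean 11, SD 5.5) failed in 11% at n = 96, 40% at n = 192 and 95% at n = 320. What is tested matters too: simulated PHQ-9 change scores failed in 6-49% at n = 96.

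**Step 3. What does the fallback test?** Subtract each participant's own mean over the k = 4 visits, rank all kN aligned values together, and let R_j be the rank sum of visit j and R_i that of participant i:

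T = (k−1)·[ΣR_j² − (kN²/4)(kN+1)²] / [kN(kN+1)(2kN+1)/6 − ΣR_i²/k], referred to χ² with k−1 = 3 df.

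Treatment group appears nowhere in T. Relabelling every participant's arm leaves T and its P value unchanged.

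**Step 4. What follows numerically?** Simulations with 48 per arm; rejection at 0.05.

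| Assumed data | Truth | Mixed ANOVA interaction | Friedman aligned ranks |
|---|---|---|---|
| Skewed PHQ-9 | both arms fall 15% | 5-6% | 62% |
| Skewed PHQ-9 | both arms fall 30% | 5-6% | 100% |
| Skewed, zero-heavy counts | no change in either arm | 5.9% | 4.6% |
| Skewed, zero-heavy counts | both arms fall 30% | 6.0% | 85.4% |
| Skewed, zero-heavy counts | arms fall 40% and 20% | 19.7% | 86.2% |

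The count rows only illustrate how the tests behave, since the plan writes no such fallback for between-arm counts. The last two rows show the problem most directly: the aligned-ranks test rejects at almost the same rate whether or not the arms differ. The mixed ANOVA stays near its nominal size on skewed data, so failing a normality check is not by itself a reason to leave it.

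**The case against.** Naming a rank alternative in advance is conventional, and the outcomes affected are limited: PHQ-9 is secondary, and the Objective 1 switch concerns an uncontrolled before-after comparison in one arm. Histograms accompany Shapiro-Wilk and no cut-off is given, so it is not stated that Shapiro-Wilk alone decides; thresholds may sit in an analysis plan that is not shown. All of this stands, but none of it cures a named fallback without a group term.

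A reader might infer more than the text supports:

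- **That the analysis the trial was sized for is displaced for consumption.** The effect size is for substance use, and Objective 3 writes no fallback for between-arm consumption. Displacement follows only from reading the Abstract's general rule, or the word that links the two sentences in Objective 3, broadly. What can be said is that the rule is unclear.
- **That results could not be given in PHQ-9 points or days of use.** Mean changes with confidence intervals are planned in each arm without a normality condition.
- **That choosing the test from the data spoils the P value.** A two-stage simulation (Shapiro-Wilk, then t test or Wilcoxon-Mann-Whitney) gave type I error of 4.9-5.5%, against 5.0-5.6% for the t test alone. With those proxy tests, mean and rank results disagreed in only 2-6% of simulated trials. The harm comes from which fallback is named, not from the two-stage choice itself.
- **That PHQ-9 will almost always fail.** This is well supported for 28-day counts; for PHQ-9 it depends on case mix.
- **That Objective 2 or GAD-7 is affected.** Neither has a gated test.

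**Conclusion.** The point holds in a limited form. For between-arm PHQ-9, a normality check on the variable can replace the group-by-time test with one that, in its usual form, tests time alone. With no group difference, the fallback rejected in 62% of simulated trials after a common 15% fall and in 100% after a common 30% fall, against 5-6% for the interaction it replaces. The chance that the switch is used is about 33-100% at n = 96 for the skewed PHQ-9 shapes examined, and lower if the scores are close to normal.

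The Objective 1 switch has the same misdirected check, with less at stake. For between-arm consumption the defect is one of clarity only.

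The conclusion that the fallback lacks a group term does not depend on simulation. It does assume the usual form of the test, with participants as blocks and visits as conditions; if another version that tests group by time is meant, the protocol should say so. The sizes rest on assumed distributions, 48 per arm and complete data.

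**What to change.** - Remove the normality-based choice of test from the Abstract (Methods) and from Specific Objectives 1 and 3.
- State in Objective 3 that the mean-based group-by-time analysis is used for between-arm consumption and PHQ-9 whatever the distribution, with robust (sandwich) or bootstrap standard errors.
- State in Objective 1 that a mean-based analysis is used for within-arm consumption.
- Keep histograms and Shapiro-Wilk as description only.
- Prespecify one sensitivity analysis suited to skewed, bounded outcomes that tests the difference between arms, for example an ordinal or negative binomial model with a group-by-time term. It should be reported whatever the main analysis shows.

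The cost is wording and one extra analysis, with no new data or visits. The Abstract (Results) says that recruitment continues and that no analyses have been done, so the change can still be made before outcome data are examined.

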### Study Design

The design of this study corresponds to a superiority randomized controlled clinical trial, conducted in public primary care clinics, to evaluate the effect of an SFBI and compare it with usual care, consisting of brief counseling and an educational brochure. The experimental and control groups will consist of primary care patients who report intermediate- to high-risk substance use and will be randomly assigned to each group. In addition, the acceptability and relevance of the applied intervention will be explored among participants in the experimental group using a qualitative approach, which focuses on a deep understanding of experiences considering the subjectivity and meanings attributed to them by individuals [34], through focus groups and qualitative analysis of their content. This study is guided by the SPIRIT (Standard Protocol Items: Recommendations for Interventional Trials) checklist (Multimedia Appendix 1).

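### Objective 3 makes its mixed ANOVAs 1-tailed, but the group-by-time F-test the trial was sized on has no direction, and the Friedman fallback does not compare the arms

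*Protocol article*

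**What the plan says.** The Study Design section states that "The design of this study corresponds to a superiority randomized controlled clinical trial". For Objective 3 the Analysis Plan sets the threshold: "we will use the standard *P*<.05 criterion to make inferences". Within Specific Objective 3 it then adds: "Given that this is a superiority design, 1-tailed tests will be used for the following comparisons".

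Three comparisons follow that sentence:
- a mixed ANOVA on monthly consumption, "with group (experimental and control) as the between-subjects factor" and four measurement times (pretreatment, 3, 6 and 9 months) as the within-subjects factor;
- a mixed ANOVA of the same form on PHQ-9, "with the Friedman-aligned ranks test applied if the variable normality assumption is unmet";
- a Fisher exact test on the percentage who reduce use and risk.

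Specific Objective 3 does not name the ANOVA effect that answers the question. The Sample Size section does: "For the interaction effect between within-subject and between-subject factors in mixed ANOVA", with an effect size of d=0.24 ("equivalent to Cohen *f*=0.12"), "considering 80% power and a significance level of 5"%, giving 96 evaluable. This becomes 160 after 40% attrition, and 320 are to be recruited because the evaluation is done separately by substance.

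**The concern.** A 1-tailed test needs a signed statistic. The group-by-time interaction over four visits has 3 numerator degrees of freedom and no sign, so the 1-tailed rule cannot be carried out on the effect the trial was sized to detect. The analyst would have to choose after the fact between ignoring the rule, halving the P value, or picking some other contrast.

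The fallback has a different fault. The Friedman aligned-ranks test compares repeated measurements within blocks. With participants as blocks and visits as the repeated factor, it tests change over time in both arms pooled. Every participant receives brief counselling before randomisation (Data Collection), so improvement in both arms is plausible, and that is the pattern the fallback would flag. At stake is whether a significant Objective 3 result on consumption or PHQ-9 says anything about SFBI against control.

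**Working it through.** **Inputs.** From the protocol: 2 groups, 4 times, f=0.12, d=0.24, alpha 0.05, 80% power, 96 evaluable, 40% attrition, 320 recruited. Assumed, because the article gives neither: correlation ρ=0.5 between visits (varied below) and sphericity. Balanced arms are inferred from the randomisation text.

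**1. Degrees of freedom.** (2−1)×(4−1) = 3.

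**2. The plan's own figure.** For a within-between interaction, λ = f²·N·m/(1−ρ) = 0.0144×96×4/0.5 = 11.06, on 3 and 3×(96−2) = 282 df. At alpha 0.05 power is 80.0%; at N=94 it is 79.1%. So 96 reproduces, and 96/0.6 = 160. With the same F-test at alpha 0.10, the only mechanical way to halve its P value, N would be 78. The planning therefore used the ordinary non-directional 5% test.

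**3. Direction.** Let the arms differ by 0 at baseline and δ SD at each follow-up. Then λ = (N/4)·Σ(δⱼ−δ̄)²/(1−ρ) = (N/4)(0.75δ²)/(1−ρ). Only δ² enters, so the sign is lost.
- N=192 (320×0.6), δ=±0.4: λ = 48×0.12/0.5 = 11.52, rejection 82% whether SFBI is better or worse.
- N=96, δ=±0.4: λ = 5.76, rejection 49% either way.
- Simulation, N=96, 20,000 runs: 66.6% when SFBI is better by 0.48 SD and 65.7% when it is worse by 0.48 SD.

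**4. The fallback.** The aligned-ranks statistic subtracts each participant's own mean, ranks all residuals together and sums ranks by visit. Group appears nowhere. Simulated rejection at nominal 5% (48 per arm, ρ=0.5):

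| Scenario | Aligned-ranks test rejects |
|---|---|
| No change in either arm | about 5% |
| Both arms improve 0.3 SD, no group difference | 85% |
| SFBI better by 0.24 SD, control flat | 18% |
| Arms move 0.4 SD in opposite directions | 4% |

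In the last row the interaction F rejects 98.8%.

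**5. A signed replacement.** Take the mean of the three follow-ups minus baseline, SFBI minus control. Its variance per participant is 1+(1+2ρ)/3−2ρ = 0.667 at ρ=0.5 (SD 0.816). For a constant 0.24 SD effect:
- N=96: z = 0.24/(0.816×√(2/48)) = 1.44; two-sided 5% power Φ(1.44−1.96) = 30%.
- N=192: z = 0.24/(0.816×√(2/96)) = 2.04; power 53%.
- The 3-df F for the same pattern has λ = 2.07 and 4.15, so power of 20% and 37%.

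Over ρ = 0.3 to 0.7, the signed contrast has 23% to 46% power at N=96 and 41% to 75% at N=192; the 3-df F has 15% to 31% and 27% to 58%. At ρ=0.5, 80% power needs 182 per arm two-sided or 144 per arm one-sided.

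These figures sit far below 80% because a constant 0.24 SD difference gives an interaction f of √(0.75×0.24²/16) = 0.052, not 0.12.

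**The case against.** Several points on the other side stand.

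- A reader might infer that superiority cannot be tested at all. The documents do not support that. The Fisher exact comparison falls under the same 1-tailed rule and is validly directional. A 1-df group main effect could also be signed, although the text does not select it and it would average in the baseline visit.
- A reader might infer that the fallback undermines the primary outcome. The fallback clause sits in the PHQ-9 sentence, and PHQ-9 measures a secondary outcome. Whether it extends to consumption is unclear.
- A declared 1-tailed 5% level, with the direction stated in the Hypotheses, has the error rate it declares. Preferring 2.5% in the direction of benefit is partly convention. What is weak is the reason given, since a superiority aim does not by itself imply 1-tailed testing.
- A reader might infer that alpha is really 10%, or that harm would be reported as superiority. The protocol nowhere says the F-test P value will be halved. It also requires mean change with a CI in both arms at each follow-up, where the direction would be visible.
- The 82% rejection figure uses 192 evaluable and a 0.4 SD difference. At 96 evaluable it is 49%. The loss of sign does not depend on either choice.

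None of this gives the 1-tailed rule a meaning for the interaction F-test, or puts a group factor into the Friedman test.

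**Conclusion.** The point holds in two specific places. First, the 1-tailed rule is undefined for the group-by-time interaction, the effect on which the trial was sized. That test treats benefit and harm alike, and N=96 matches only its ordinary 5% form. This affects the ANOVAs on consumption, the primary outcome domain, and on PHQ-9. Second, the nonparametric fallback tests time in both arms pooled, not SFBI against control. On the plain reading this concerns PHQ-9 only.

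The Fisher exact comparison is sound in this respect, and 96 is not an arithmetic error. The absence of direction and of a group factor follows from the form of the tests and needs no assumption. The percentages rest on an assumed correlation of 0.5, equal variances, normal data in the simulations and a constant effect over follow-ups.

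**What to change.** For consumption and for PHQ-9, replace the 1-tailed interaction test with one prespecified signed 1-df contrast: SFBI minus control in change from baseline, either averaged over 3, 6 and 9 months or at one named visit. State its alpha and sidedness; two-sided 5% with a 95% CI is the conventional choice. Replace the Friedman fallback with a method that keeps the same group contrast, such as a rank or permutation test on change scores between arms, and say which outcomes it covers. The Fisher comparison can stay, with its sidedness stated.

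The cost is more than wording, because the 80% power statement belongs to the 3-df test at f=0.12 and must be restated for the new contrast. With a constant 0.24 SD effect and correlation 0.5, two-sided power is about 30% at 96 evaluable and 53% at 192. That is still better than the 3-df test for the same pattern, so the change exposes a shortfall and does not create one. The article reports that no analyses have been conducted and that recruitment runs to December 2026, so the change can be made before any results are seen.

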#### Treatment Outcome Profile

This instrument has been validated in Chile [41] and was originally developed by the National Treatment Agency for Substance Misuse [42]. It is used to obtain comparable data and goals regarding improvements of individuals with substance use after treatment. It consists of 3 sections: substance use in the past 4 weeks, offensive behavior (social norms such as theft, drug dealing, fights, and domestic violence), and physical and psychological health, including quality of life, work, education, and housing. In total, there are 17 questions. It will be administered at baseline and follow-ups.

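### The primary outcome is not tied to one variable or one test: within each substance, two between-arm comparisons can each support a superiority claim at P<.05

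*Protocol article*

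**What the plan says.** All references are to the protocol article.

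- **Abstract, Methods.** "The primary outcome assessed will be substance use patterns". No instrument item, unit or visit is attached.
- **Treatment Outcome Profile (TOP).** One of its three sections covers "substance use in the past 4 weeks".
- **Analysis Plan, opening paragraph.** For Objective 3, "we will use the standard *P*<.05 criterion to make inferences".
- **Specific Objective 1, experimental arm only.** "the change in frequency and quantity of consumption according to the TOP instrument will be calculated for each participant", followed by a repeated-measures ANOVA for a "significant treatment effect on the average weekly consumption".
- **Specific Objective 3, between arms.** "Given that this is a superiority design, 1-tailed tests will be used for the following comparisons". Two comparisons of substance use follow. The first is "The mean decrease in monthly consumption will be compared between individuals in the experimental and control groups using a mixed ANOVA", with four measurement times as the within-subjects factor. The second, last in the list, is a Fisher exact test of the percentage who reduce their use patterns and risk.
- **Sample Size.** The calculation is for the interaction in the mixed ANOVA, "considering 80% power and a significance level of 5" percent. It gives 96 participants, or 160 after 40% attrition. Evaluation is to be separate by substance type.

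No ranking of these tests and no adjustment for having more than one is stated.

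**The concern.** A superiority trial needs one between-arm test per primary claim, fixed in advance. Here the primary outcome is a construct, and the plan offers two tests of it.

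Two things are left open. The first is the variable. Monthly consumption could mean days of use in the recall window or the amount used, and Objective 1 mentions both frequency and quantity. Two analysts following the text could build different variables and get different P values.

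The second is the test. A positive ANOVA with a null Fisher test, or the reverse, could each be reported as success on the primary outcome. The 5% level would then describe each test but not the claim. This arises within one substance, before any question of testing several substances.

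**Working it through.** **1. The plan's own figure.** Inputs from Sample Size: Cohen f = 0.12, α = 0.05, power 80%. From Objective 3: 2 groups and m = 4 measurements. Assumed, because not stated: correlation between repeated measures ρ = 0.5, and sphericity.

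- λ = f² × N × m / (1 − ρ) = 0.0144 × 96 × 4 / 0.5 = 11.06
- df1 = (2 − 1)(4 − 1) = 3; df2 = (96 − 2)(4 − 1) = 282
- Power from the noncentral F = 0.800, and 96 is the smallest N that reaches 80%
- Attrition: 96 / (1 − 0.40) = 160

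Both stated figures reproduce. The calculation spends the whole 5% on one test, the interaction.

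**2. Between-arm tests of substance use in Objective 3, for one substance.**

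| Comparison | Variable | Visits | Called primary? |
|---|---|---|---|
| Mixed ANOVA | monthly consumption; days or quantity not stated | all four times in one test | no |
| Fisher exact | percentage reducing use and risk | not stated | no |

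The Objective 1 analyses use the experimental arm only, so they are not in this table.

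**3. Chance of at least one false positive with two tests at 5%.**

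- Independent: 1 − 0.95² = 0.0975
- Correlated, by simulation of one-sided normal statistics (400,000 draws): 0.089 at correlation 0.5 and 0.075 at 0.8

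The correlation is an assumption, so the range is 7.5% to 9.75%. Treating both tests as one-sided normal statistics of exact 5% size is an approximation. Fisher's test is conservative, and an interaction F test on 3 degrees of freedom has no direction of its own.

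**4. If the Fisher test is repeated at 3, 6 and 9 months.** This is an assumed reading. The per-visit phrase opens the list of change calculations, while the Fisher test comes later with no visit given. With 1 + 3 = 4 tests:

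- Independent: 1 − 0.95⁴ = 0.185
- Correlation 0.5: 0.145; correlation 0.8: 0.106

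**5. Price of keeping both tests as equal routes to success.** Bonferroni sets α = 0.05 / 2 = 0.025. Power of the interaction test at N = 96 falls from 0.800 to 0.713. Restoring 80% needs N = 114, and 114 / 0.60 = 190 after attrition, for each substance evaluated. With one designated test, N stays at 96 (160).

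**The case against.** The best reply is that a lead analysis can be identified. The sample size is computed for the mixed-ANOVA interaction and points to the Analysis Plan, where that ANOVA is the first one-tailed comparison listed. This stands as a strong hint, and it is why the fix builds on that test. But the article never calls it primary, never ranks the Fisher test below it, and does not say which consumption variable it uses.

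A reader might also infer stronger faults that the text does not support:

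- **Superiority on frequency or quantity at any of three visits.** Frequency and quantity, and weekly consumption, are analysed only within the experimental arm, which cannot show superiority over usual care. Between arms, the mixed ANOVA is one test over all visits. The per-visit items in Objective 3 are changes and means with confidence intervals, with no stated between-arm test of means.
- **Weekly and monthly consumption as conflicting endpoints.** If both come from the same item over the TOP's 4-week window, they differ by a constant factor of 4, which leaves ANOVA and rank tests unchanged. The wording should be aligned, but the real gap is days versus quantity.
- **No common unit across substances.** Sample Size says that evaluation is separate by substance type, so no sum across substances is planned.

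It could also be said that endpoint detail belongs in a separate analysis plan. That would answer silence. Here the article itself sets out two tests of the primary outcome at P<.05.

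**Conclusion.** The point holds in a limited form. The primary outcome is not fixed as one variable, and Objective 3 gives it two unranked one-tailed comparisons at P<.05. Within one substance, the chance of at least one false positive is about 7.5% to 9.75% rather than 5%, for correlations of 0.8 to 0. If the Fisher test is repeated at three visits, it is about 10.6% to 18.5% over the same correlations. These figures rest on the assumed correlations and on treating each test as having exact 5% size. Multiplicity across substances is a separate matter and is not counted.

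The uncertainty about days or quantity needs no simulation: the text allows either, so the primary result is not determined by the plan. The sample size is not at fault, because it already assumes one test.

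**What to change.** 1. Define consumption as one TOP item in one unit that matches its 4-week recall, for example days of use in the past 4 weeks, for each substance evaluated.
2. Use that variable in Objectives 1 and 3, in place of both weekly and monthly consumption.
3. Designate the mixed-ANOVA group-by-time interaction as the single primary test for each substance.
4. Make the Fisher comparison, quantity and any per-visit contrasts secondary, and state the visit or visits for the Fisher test.

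This keeps the evaluation by substance and the test behind N = 96. Moving to one index substance or a single visit is not needed: the first would replace the by-substance evaluation, and the second would drop the interaction test on which the sample size rests.

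The cost is wording in the protocol, the analysis plan and the registry entries. ClinicalTrials.gov registration is still pending, and the existing Open Science Framework entry should be updated. The TOP is already scheduled at all four visits. Recruitment has begun but no analyses have been conducted, so the change should be dated to show that it came before any look at outcomes by arm. The downside is that the Fisher result, quantity and single visits can no longer support a primary superiority claim.
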